## Abstract

**Background:**

Family members of critically ill patients experience symptoms of postintensive care syndrome-family (PICS-F), including anxiety, depression, and posttraumatic stress disorder. Postintensive care syndrome-family reduces the quality of life of the families of critically ill patients and may impede the recovery of such patients. Cognitive behavioral therapy has become a first-line nonpharmacological treatment of many psychological symptoms and disorders, including anxiety, depression, and posttraumatic stress. With regard to managing mild-to-moderate symptoms, the delivery of cognitive behavioral therapy via mobile technology without input from a clinician has been found to be feasible and well accepted, and its efficacy rivals that of face-to-face therapy.

**Objective:**

The purpose of our pilot study is to examine the efficacy of using a smartphone mobile health (mHealth) app to deliver cognitive behavioral therapy and diminish the severity and prevalence of PICS-F symptoms in family members of critically ill patients.

**Methods:**

For our pilot study, 60 family members of critically ill patients will be recruited. A repeated-measures longitudinal study design that involves the randomization of participants to 2 groups (the control and intervention groups) will be used. The intervention group will receive cognitive behavioral therapy, which will be delivered via a smartphone mHealth app. Bandura’s social cognitive theory and an emphasis on mental health self-efficacy form the theoretical framework of the study.

**Results:**

Recruitment for the study began in August 2020. Data collection and analysis are expected to be completed by March 2022.

**Conclusions:**

The proposed study represents a novel approach to the treatment of PICS-F symptoms and is an extension of previous work conducted by the research team. The study will be used to plan a fully powered randomized controlled trial.

**Trial Registration:**

ClinicalTrials.gov NCT04316767; https://clinicaltrials.gov/ct2/show/NCT04316767

**International Registered Report Identifier (IRRID):**

DERR1-10.2196/30813

## Introduction

### Background

Nearly 6 million patients are admitted to the intensive care unit (ICU) each year in the United States [1]. Although the majority of patients leave the ICU after a brief stay, 20% to 39% of these patients require mechanical ventilation and a potentially prolonged stay [2]. Family members of these critically ill adult patients are at risk for developing clinically significant psychological distress. Such distress is called postintensive care syndrome-family (PICS-F), and it includes symptoms of anxiety, depression, posttraumatic stress, complicated grief, and a diminished quality of life [3-10]. The prevalence of PICS-F symptoms can be as high as 69% within the first 6 months of ICU hospitalization and has been documented up to 4 years after the development of ICU illness across transitions of care to other facilities [4-6,9,11-17]. The identification and treatment of PICS-F symptoms across the continuum of recovery has been recognized and promoted by the Society of Critical Care Medicine—the leading critical care organization in the United States. Further, many experts have emphasized the need to address the gaps between transitions of care [8,18,19]. PICS-F reduces the quality of life of critically ill patients’ families and may impede the recovery of such patients [9,11,20]. Many family members of critically ill patients are called upon to provide informal caregiving during the prolonged recovery phase, which is associated with significant physical and emotional burdens [21-23]. The overall costs to society of anxiety, depression, and posttraumatic stress symptoms associated with PICS-F have not been calculated but are likely to be considerable, given the billions of dollars associated with managing the symptoms of these disorders [24-26].

A variety of strategies and interventions have been proposed to support family members during and after critical illness development, including post-ICU clinics, improved communication strategies, ICU diaries, family ICU navigators, and proactive palliative care and ethics consultation, but they have had mixed results [16,17,27,28]. A randomized controlled study of a clinician-led telephone- and web-based coping skills training program showed no improvement in psychological distress symptoms among patients and family members compared with an education program [29]. The intervention was implemented after the ICU patient and family member dyads were discharged to home, which often occurred well after the development of acute critical illness. The implementation of these clinician-led interventions requires at least moderate logistical, personnel, and financial resources and may be limited across interinstitutional transitions of care. Furthermore, family members of ICU patients are not patients themselves, and the medical services rendered to them are not currently billable. This has resulted in an inadequate medical system infrastructure for the assessment and treatment of PICS-F [10]. Therefore, effective interventions for PICS-F symptoms need to directly address the symptoms experienced by family members, be portable and longitudinal in terms of their scope for family members across transitions of care, and be made available on demand for family members while limiting the hospital resources required to implement and sustain the intervention. Strong empirical support for sustainable interventions that aim to prevent or diminish PICS-F symptoms is currently lacking.

Cognitive behavioral therapy (CBT) is a form of therapy that emphasizes cognitive and behavioral strategies for correcting unhelpful appraisals of stressful events and mitigating their influence on feelings and active coping behaviors for responding to distress [30]. CBT has become the first-line nonpharmacological treatment for the symptoms of a growing list of mental health problems, including depression, anxiety, posttraumatic stress, substance abuse, and eating disorders [31]. CBT programs delivered via mobile health (mHealth) solutions have been shown to be efficacious, cost-effective, and well accepted by individuals with mild-to-moderate symptoms of depression, anxiety, and posttraumatic stress [32-35]. Due to the development and rapid market growth of smartphone technology, mHealth apps that deliver CBT have also demonstrated significant efficacy in treating a variety of symptoms, including anxiety, depression, and posttraumatic stress [36-41]. Self-efficacy appears to be an important concept for understanding treatment gains in CBT therapy and chronic disease self-management [42-48]. Investigators have reported that the concept of self-efficacy mediates the effect between web-based and mobile CBT interventions and improvements in symptoms of stress, anxiety, and depression [49,50]. However, despite the empirical support for its effectiveness in other populations, the efficacy of delivering CBT to family members with PICS-F symptoms via mHealth technology has not been examined.

### Theoretical Framework

The theoretical basis for the proposed study is Bandura’s social cognitive theory, which describes human functioning as a reciprocal interplay among personal, behavioral, and environmental factors [51]. Perceived self-efficacy—an individual’s belief that they can perform a behavior—is a central cognitive tenet of the theory and has been identified as an important factor for explaining treatment success in CBT, the self-management of chronic conditions, and improved psychological functioning [42-48,52]. Mental health self-efficacy (MHSE)—a person’s confidence in managing his or her mental health symptoms—is a self-efficacy construct that was developed based on Bandura’s guidelines for constructing self-efficacy questionnaires and was found to be a significant mediator for the beneficial treatment outcomes of a mobile phone CBT intervention for mild-to-moderate depression, anxiety, and stress [49]. Furthermore, self-efficacy is likely to be an important factor in mobile CBT interventions with minimal therapist input, given the central role of individuals in self-monitoring and problem solving.

### Study Aims

The findings from our pilot study will allow for the collection of preliminary data that are needed for planning a fully powered randomized controlled study. The specific study aims are as follows: (1) determine the prevalence and severity of PICS-F symptoms (anxiety, depression, and posttraumatic stress), health-related quality of life (HRQOL), and MHSE in family decision makers of critically ill patients and their changes over time (at enrollment, 30 days after enrollment, and 60 days after enrollment); (2) determine differences in PICS-F symptom severity, HRQOL, and MHSE between family decision makers (ie, those of critically ill patients) receiving an mHealth app intervention and family members receiving standard care and support; and (3) determine the relationship between the dose of the mHealth app (total time spent with the app and the total number of log-ins) over the course of the study (60 days) and changes in PICS-F symptom severity (anxiety, depression, and posttraumatic stress), HRQOL, and MHSE.

## Methods

### Design

A repeated-measures longitudinal study design that involves the randomization of participants to 2 groups (the control and intervention groups) will be used. A research assistant will randomize study participants by using computer-generated random numbers after study enrollment is completed and baseline measurements are obtained.

Previous work conducted by [name] and colleagues [6,7,9,11] has laid the descriptive groundwork for the proposed study. The research team has recently completed a longitudinal feasibility study at Summa Health in which they examined the implementation of the mHealth app delivery of CBT to family decision makers of critically ill patients. The data from the feasibility study was used to directly inform the methodology of the proposed pilot study. The usage of the app was encouraging, and the findings of the feasibility study have been accepted for publication [53].

### Sample and Setting

The study will include family members of critically ill patients who are admitted to 1 of 2 26-bed ICUs at the Akron campus of Summa Health. A family member will be defined as a person who would be the most involved in a patient’s treatment and care decisions; the person does not need to be a blood relative. A sample size of 60 family members is planned for our pilot study (intervention group: n=30; control group: n=30). The sample size was determined according to the recommendations of Whitehead et al [54] for estimating an a priori small effect size, and an attrition rate of 30% was derived from previous studies [6,9].

### Inclusion Criteria

The inclusion criteria are as follows: (1) individuals aged 18 years or older; (2) individuals who self-identify as the family decision maker of the critically ill patient; (3) individuals who can read and speak English; (4) individuals who own a smartphone with an iOS or Android operating system; (5) family members of critically ill patients who have been in the ICU for more than 3 days; (6) family members of critically ill patients who are being mechanically ventilated and lack cognitive capacity; (7) family members of critically ill patients who are not expected to be transferred out of the ICU within 48 hours after the identification of their inclusion in the study; and (8) family members of critically ill patients aged 18 years or older. These inclusion criteria have been used in previous studies conducted by the principal investigator and other researchers [6,9,55].

### Instruments

#### Demographic Form

The information obtained from the demographic form will be collected from study participants and medical records. Data about family members’ characteristics will include demographic data, a history of treatment for psychiatric disorders (anxiety, depression, and posttraumatic stress disorder [PTSD]), a history of taking prescription medications for emotions or moods, and a history of previous ICU-related decision-making experience. Data about patients’ characteristics will include demographic data, the length of ICU stay, the duration of mechanical ventilation, admitting ICU diagnoses, baseline medical comorbidities, the baseline severity of illness, and disposition at each study time point (T).

#### Hospital Anxiety and Depression Scale

Symptoms of anxiety and depression will be assessed by using the 14-item Hospital Anxiety and Depression Scale (HADS) instrument [4,17,56,57]. The HADS is a 14-item scale with 7 items that form an anxiety subscale (HADS-A) and 7 items that form a depression subscale (HADS-D). Each of the two subscales can have scores that range from 0 to 21. Higher scores indicate higher levels of anxiety or depression symptoms. A cutoff score of ≥11 is consistent with moderate-to-severe symptoms of anxiety or depression.

#### PTSD Checklist for the Diagnostic and Statistical Manual of Mental Disorders, Fifth Edition

Symptoms of posttraumatic stress will be measured by using the 20-item PTSD Checklist for the *Diagnostic and Statistical Manual of Mental Disorders, Fifth Edition* (PCL-5) instrument [58]. The PCL-5 is a 20-item self-report measure that corresponds to the *Diagnostic and Statistical Manual of Mental Disorders,*
*Fifth Edition* criteria for PTSD [59]. A total symptom severity score (range 0-80) can be obtained by summing all of the items’ scores. Higher scores indicate a higher severity of PTSD symptoms. A cutoff score of 31 or higher is the recommended indicator for a provisional diagnosis of PTSD.

#### Medical Outcomes Study 12-item Short-Form General Health Survey

The Medical Outcomes Study 12-item Short-Form General Health Survey is a 12-item self-report scale for measuring HRQOL [60,61]. Each item on the scale is scored by using a Likert-type scale. Raw scores are transformed to scores that range from 0 (worst) to 100 (best). The scale provides a summary score of 0 to 100 for the physical and mental health quality of life. Higher scores represent a more positive quality of life.

#### MHSE Scale

The MHSE Scale is a 6-item scale for measuring MHSE [49]. Each item is measured on a 10-point Likert scale that ranges from 1 (not at all confident) to 10 (totally confident). Items are summed to obtain a total score that ranges from 6 to 60. Higher scores indicate higher levels of MHSE.

### Intervention

The selection of the mHealth app was based on several criteria, as follows: (1) the app uses principles of CBT to deliver strategies for managing stress, anxiety, and depression; (2) the app is available for Android and iOS operating systems; and (3) there is a free version of the app that participants can use after the proposed study. Based on these criteria, the Sanvello (formerly known as Pacifica) app developed by Sanvello Health was chosen [62]. Sanvello has been identified as a well-designed app that is based on CBT principles, has been selected as the app of choice for other trials that have examined the implementation of the mHealth app delivery of CBT, and has been shown to be efficacious in diminishing mild-to-moderate symptoms of anxiety and depression in community samples of adults [41,63,64].

The Sanvello app is a mobile app that is marketed as a tool that provides on-demand help for managing anxiety, stress, and depression. It includes a suite of tools that are based on CBT and mindfulness principles that teach users strategies for self-managing stress, mood, anxiety, and depression. Upon initial log-in, the app asks users to select up to 3 of a possible 8 goals to work on and prompts users daily to rate their mood. Based on their mood ratings, the app suggests several activities for addressing users’ moods. The app guides users through a variety of short audio lessons or branched sessions based on their moods or goals and allows users to monitor their progress. Exercises typically take 3 to 5 minutes to complete. There is an anonymous peer support community in which users may post their thoughts and struggles as well as find listings of crisis lines and resources for users in emergency situations.

Upon randomization to the intervention group, family members will be assisted with downloading the app and creating a Sanvello account. Study participants will receive an introductory training session and instructional guidebook for reviewing basic app usage and the app’s components. Study participants will be instructed to start their mHealth app usage with the first “guided journey” module, which is called “feeling better.” The “feeling better” module has 7 individual exercises, and participants will complete 1 exercise each day. Once the entire “feeling better” module is completed, the participants will be encouraged to continue to complete the remaining “guided journey” modules—“braving anxiety,” “becoming mindful,” “taking control,” and “building confidence.” These remaining modules are composed of 6 to 11 individual exercises. Additionally, participants will be allowed to use the components of the mHealth app in whichever way they want. This includes accessing tools that allow users to track their exercise and sleep habits; communicating with web-based coaches; and sharing experiences in a nonjudgmental, web-based, and secure forum. Participants will receive weekly text reminders that encourage them to use the mHealth app. At the conclusion of the study, app usage data (the number of log-ins, time spent with the app, etc) will be collected and provided to the research team by Sanvello via an encrypted, password-protected, and deidentified data file.

### Recruitment

The research assistant will visit the ICU 3 times per week to identify newly admitted patients who are eligible for the study. The research assistant will screen for eligibility by using medical records and consulting with the health care team. If the eligibility criteria are met by a family member, they will be approached for enrollment within the first week after patient admission. The research assistant will consult with the bedside nurse to identify eligible family members while visiting patients or will contact eligible family members by phone. Family members will be randomized to the intervention group or control group after enrollment and data collection at enrollment are complete.

The longitudinal study design has 3 data collection points. Data will be collected by using the same methods as those in a previous study conducted by [name] and Martin [9] upon enrollment into the study (T1), 30 days after study enrollment (T2), and 60 days after study enrollment (T3). The data collection process for each time point is shown in Table 1. At 30 and 60 days after study enrollment, family members will be contacted by phone, email, or standard mail. Participants’ preferences for follow-ups will be identified upon their enrollment into the study. A US $30 gift card will be offered at T1 and T2, and a US $50 gift card will be offered during follow-up data collection in T3 for a possible total of US $110.

**Table 1 table1:** Data collection checklist.

Data collected	T1^a^ (Enrollment)	T2^b^ (30 days after enrollment)	T3^c^ (60 days after enrollment)
Demographic data	✓	✓	✓
Hospital Anxiety and Depression Scale score	✓	✓	✓
PCL-5^d^ score	✓	✓	✓
Mental Health Self-Efficacy Scale score	✓	✓	✓
SF-12^e^	✓		✓
Mobile health app usage			✓

^a^T1: time point 1.

^b^T2: time point 2.

^c^T3: time point 3.

^d^PCL-5: Posttraumatic Stress Disorder Checklist for the *Diagnostic and Statistical Manual of Mental Disorders, Fifth Edition.*

^e^SF-12: Medical Outcomes Study 12-item Short-Form General Health Survey.

### Data Analysis and Statistical Plan

Data will be analyzed by using SPSS, version 25 (IBM Corporation), and descriptive statistics will be used to assess the frequencies and variability of the data, coding inaccuracies, outliers, and missing data. The statistical plan for each specific aim is detailed in the following subsections.

#### Aim 1

We will report study variables with descriptive statistics. Changes over time will be examined with a repeated-measures analysis of variance.

#### Aim 2

Differences between the intervention and control groups will be assessed with a two-tailed Student *t* test. Differences between groups with regard to the severity of PICS-F symptoms will be used to calculate the effect size for the intervention.

#### Aim 3

The relationship between total mHealth app doses and longitudinal changes in study variables will be examined with a Pearson correlation analysis.

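### Aim 1's repeated-measures ANOVA names no arm term, so change after randomisation is averaged over both arms, and by default it leaves out anyone with a missing visit

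*Protocol article*

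**What the plan says.** All references are to the protocol article.

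- **Study Aims.** Aim 1 covers symptoms, quality of life and mental health self-efficacy "in family decision makers of critically ill patients and their changes over time (at enrollment, 30 days after enrollment, and 60 days after enrollment". The group is not split by arm.
- **Data Analysis and Statistical Plan, Aim 1.** There are two sentences. The first reports the study variables descriptively. The second reads: "Changes over time will be examined with a repeated-measures analysis of variance". No between-subjects factor is named.
- **Data Analysis and Statistical Plan, Aim 2.** The arm comparison stands apart: "Differences between the intervention and control groups will be assessed with a two-tailed Student" *t* test. The effect size for the intervention comes from here.
- **Sample and Setting.** "A sample size of 60 family members is planned for our pilot study (intervention group: n=30; control group: n=30"), and "an attrition rate of 30% was derived from previous studies".
- **Recruitment.** Participants are randomised once enrollment data are collected, so T2 and T3 both follow randomisation. Table 1 has HADS, PCL-5 and the self-efficacy scale at T1, T2 and T3, and the SF-12 at T1 and T3 only.
- **Missing data.** They are to be looked at descriptively. No handling rule is given, and SPSS version 25 is the named software.

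**The concern.** Two features of the named method matter.

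**Pooling.** Up to T1 nobody has been allocated, so one group is right. After T1 half the sample is offered the app. A within-subject time effect fitted to everyone mixes the course under usual support with the course under the app. If the arms differ, the pooled curve belongs to neither; if they move in opposite directions, it can look flat.

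**Incomplete records.** Classical repeated-measures ANOVA needs a full set of visits for the outcome being analysed and by default removes a person who lacks one. The plan itself expects 30% attrition. The model would then discard valid T1 scores, and perhaps T2 scores. If more distressed relatives are likelier to leave, it would describe change in a less distressed subset.

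The pilot is meant to supply preliminary data for a fully powered trial. Aim 1 is the only part of the plan that models change over time; Aim 2's *t* test gives a difference between arms, not either arm's course.

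**Working it through.** **Inputs from the article:** 60 participants, 30 per arm; 30% attrition; visits as in Table 1. **Assumed, not in the article:** arm-specific changes, dropout mechanism and correlations between visits.

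**1. Attrition.** 60 × (1 - 0.30) = 42 expected completers, or 21 per arm; 60 - 42 = 18 would not enter a complete-case ANOVA. This reads the 30% as cumulative loss. If instead 30% missed each of T2 and T3 independently, 60 × 0.7 × 0.7 = 29.4 would be complete. The total of 60 cannot itself be re-derived, because it rests on a cited recommendation and no numerical effect size, alpha or power is given. Nothing here depends on that.

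**2. Pooling.** With equal numbers per arm:

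pooled change = (control change + app change) / 2

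| Control (assumed) | App (assumed) | Pooled |
|---|---|---|
| 0 SD | -0.4 SD | -0.2 SD |
| +0.2 SD | -0.2 SD | 0.0 SD |
| -2 points | -4 points | -3 points |

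**3. Information lost.** Suppose 15% are lost by T2 (assumed) and 30% by T3, with no returns. Observed scores per three-visit outcome: 60 + 51 + 42 = 153. The ANOVA uses 42 × 3 = 126 and discards 27, that is 27/153 = 18%. For the SF-12, missing only T2 costs nothing, since no T2 score is planned.

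**4. Bias in change from T1 to T3.** Take unit SD at each visit, T1-T3 correlation ρ, a true change of -0.40 SD, and dropout that depends only on the T1 score. Then

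expected completer change = -0.40 + (ρ - 1) × completers' T1 mean

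A simulation of 400,000 people with overall dropout set to 30% gave:

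| ρ | Dropout log-odds per SD of T1 | Completers' T1 mean | Simulated change | Formula | Bias (SD) |
|---|---|---|---|---|---|
| 0.5 | 0 | -0.001 | -0.399 | -0.400 | 0.00 |
| 0.5 | 0.5 | -0.142 | -0.326 | -0.329 | +0.07 |
| 0.5 | 1.0 | -0.252 | -0.272 | -0.274 | +0.13 |
| 0.7 | 0 | -0.002 | -0.401 | -0.399 | 0.00 |
| 0.7 | 0.5 | -0.147 | -0.358 | -0.356 | +0.04 |
| 0.7 | 1.0 | -0.254 | -0.326 | -0.324 | +0.07 |

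The bias is zero when dropout is unrelated to severity. It is 0.07 to 0.13 SD at ρ = 0.5 and 0.04 to 0.07 SD at ρ = 0.7, in each case towards less improvement.

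**5. Does a likelihood-type analysis help?** In a second simulation at ρ = 0.5, with 31% and 29% dropout for log-odds 1.0 and 0.5, completers gave the same biases of 0.13 and 0.07 SD. Using everyone's T1 score and conditioning on it brought both to about zero.

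**6. Scale.** At ρ = 0.5 the SD of change is √(2 × (1 - 0.5)) = 1. The standard error of a mean change is 1/√42 = 0.15 SD for 42 people pooled and 1/√21 = 0.22 SD for 21 in one arm.

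**The case against.** Several points on the other side are sound.

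- **No complete-case rule is written.** A reader might infer that the plan prescribes one. It does not; the exclusion is the default behaviour of the named method. An article may also leave missing-data handling to a fuller document. What remains is that naming classical ANOVA largely fixes how partial records are used.
- **Prevalence and severity lie outside the ANOVA.** A reader might infer that about 18 baseline records disappear from Aim 1. They do not: the descriptive sentence lets every observed score be reported at each visit. The loss concerns only the model of change.
- **No arm term is named, but none is ruled out.** One summary sentence could hide a between-subjects factor. Against that, Aim 1 speaks of one cohort and the arm comparison appears only under Aim 2, so the natural reading is a pooled analysis.
- **Aim 1 is not said to give a control-arm or natural-course estimate.** A reader might conclude that the next trial would be planned on a wrong control trajectory. The article does not assign Aim 1 that role, and it takes the effect size from Aim 2. A pooled time course answers Aim 1 as worded; it is simply hard to use once half the group has been offered treatment.
- **The bias is conditional and modest.** At ρ = 0.5, even 0.13 SD is below the 0.15 SD standard error with 42 people, and the dropout mechanism is assumed.
- **A mixed model does not cure everything.** Dropout driven by something not reflected in observed scores, such as a patient's death, can still bias it.

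These points limit the size of the finding. They do not remove the averaging over arms or the default loss of partial records.

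**Conclusion.** The point holds as a moderate weakness in a stated analysis, not as a fatal error. As written, Aim 1's change over time is an equal-weight average of app users and controls after T1 and describes neither course; this follows directly from the allocation and the timing of randomisation. The named method also by default keeps about 42 of 60 participants at the planned attrition. That number is an expectation, since 30% is a planning rate.

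The loss of information follows whenever visits are missed. Bias is only possible: none if dropout is unrelated to severity, and about 0.07 to 0.13 SD if dropout rises with baseline severity at log-odds 0.5 to 1.0 per SD and the T1-T3 correlation is 0.5. It is smaller at a correlation of 0.7. The article supports neither the mechanism nor the correlations, so these figures show scale and are not predictions. It would go too far to say that the plan mandates complete-case analysis, that the Aim 1 descriptive results are distorted by the exclusion, or that a biased result is certain.

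**What to change.** Replace the second Aim 1 sentence with one on these lines: *Change over time will be estimated with a linear mixed model (SPSS MIXED, REML) with visit, arm and arm-by-visit as fixed effects and correlated errors within participant, using all available observations from all randomised participants. HADS, PCL-5 and MHSE will be modelled at T1, T2 and T3 and the SF-12 at T1 and T3. T1 will be reported for the whole sample and later visits by arm.*

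Add that the estimates allow for dropout explained by observed scores and not for dropout driven by unobserved factors.

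**Cost.** One or two sentences and slightly more analysis work. The software stays the same and no further data are needed. The price is precision: an arm-specific change rests on half as many people, so its interval is wider than the pooled one. In the complete-case illustration the standard error rises from 0.15 to 0.22 SD, a factor of √2; using partial records may recover some of this.

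### Aim 2 compares the arms with an unadjusted t test although every scale is measured before randomisation; the test is valid but gives up precision in the effect size meant for planning the next trial

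*Protocol article*

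**What the plan says.** In the protocol article, Data Analysis and Statistical Plan, the Aim 2 subsection gives one method for the randomised comparison: "Differences between the intervention and control groups will be assessed with a two-tailed Student" *t* test. No covariate is named. The text does not say whether follow-up or change scores are tested, or at which visit. The next sentence sets the use of the result: "Differences between groups with regard to the severity of PICS-F symptoms will be used to calculate the effect size for the intervention". The repeated-measures analysis of variance in the same section belongs to Aim 1 (change over time) and is not offered as the comparison of arms.

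The baseline values exist and precede allocation. Recruitment says: "Family members will be randomized to the intervention group or control group after enrollment and data collection at enrollment are complete". Design agrees, placing randomisation "after study enrollment is completed and baseline measurements are obtained". Table 1 ticks HADS, PCL-5, MHSE and SF-12 at T1. All four are repeated at T3, and all but SF-12 at T2.

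On size, Sample and Setting plans 30 per arm, "for estimating an a priori small effect size", and adds that "an attrition rate of 30% was derived from previous studies".

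**The concern.** A Student t test cannot take a covariate. If it is run on follow-up scores, it ignores what T1 says about each participant. If it is run on change scores, it uses T1 but subtracts all of it, which over-corrects whenever the baseline-to-follow-up correlation r is below 1. Regression on the T1 score uses the baseline with the weight that the data support.

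The numerical product of Aim 2 is an effect size, and the Study Aims and the abstract's conclusions say that the pilot is to help plan a fully powered trial. With few completers, chance differences between the arms at T1 will often be appreciable, and an unadjusted contrast carries part of them into that effect size. The stake is avoidable noise in a planning figure. It is not a wrong error rate.

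**Working it through.** **Inputs from the documents.** 30 per arm and 30% attrition (Sample and Setting) give 30 × (1 - 0.30) = 21 completers per arm, N = 42. The planned total of 60 cannot be reproduced, because it rests on a cited recommendation and the article gives no alpha, power, SD or numeric effect. Nothing below depends on it being right.

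**Assumptions.** The documents do not give r. I take 0.5 with a range of 0.3 to 0.7, and the same SD at T1 and follow-up. Results are in SD units.

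**Standard error of the difference, large-sample form**
- t test on follow-up scores: √(2/n) = √(2/21) = 0.309
- t test on change scores: √(2/n) × √(2(1-r)) = 0.365, 0.309, 0.239 at r = 0.3, 0.5, 0.7
- ANCOVA: √(2/n) × √(1-r²) = 0.294, 0.267, 0.220

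**Cost of estimating the slope.** With normal scores the ANCOVA variance is multiplied on average by 1 + 1/(N-4) = 1 + 1/38 = 1.026.

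| r | ANCOVA ÷ follow-up t test: (1-r²) × 1.026 | Reduction | 21 per arm is worth | ANCOVA ÷ change-score t test, large sample: (1+r)/2 | Reduction |
|---|---|---|---|---|---|
| 0.3 | 0.91 × 1.026 = 0.934 | 7% | 21/0.934 = 22 | 0.65 | 35% |
| 0.5 | 0.75 × 1.026 = 0.770 | 23% | 21/0.770 = 27 | 0.75 | 25% |
| 0.7 | 0.51 × 1.026 = 0.523 | 48% | 21/0.523 = 40 | 0.85 | 15% |

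With the slope cost included, the change-score ratios become 0.667, 0.770 and 0.872, so the reductions are 33%, 23% and 13%. ANCOVA beats the follow-up t test once r exceeds √(1 - 1/1.026) ≈ 0.16.

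A simulation of 40,000 trials with 21 per arm gave ANCOVA standard errors of 0.298, 0.269 and 0.223. The formula with the slope cost gives 0.298, 0.271 and 0.223.

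**Chance imbalance at T1.** The baseline difference between arms has SD √(2/n).
- 30 per arm: 0.258. P(|gap| > 0.3) = 2 × [1 - Φ(0.3/0.258)] = 25%
- 21 per arm: 0.309. P(|gap| > 0.3) = 2 × [1 - Φ(0.3/0.309)] = 33%

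**How much of a gap enters the estimate**
- Follow-up scores: r × gap. At r = 0.5, a gap of 0.3 SD moves the difference by 0.5 × 0.3 = 0.15 SD (0.09 at r = 0.3, 0.21 at r = 0.7).
- Change scores: -(1-r) × gap. At r = 0.5 that is -0.15 SD, in the opposite direction.
- ANCOVA: about zero. The simulated slopes on the gap were 0.01, 0.00 and 0.00.

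**The case against.** The strongest reply is that nothing here is invalid. Under randomisation the t test is unbiased, with correct type I error before attrition, and a 60-person pilot for preliminary data need not be analysed with full efficiency. The first half stands: the fault is efficiency.

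The practical gain at a small effect is also modest. With 21 per arm the 95% CI half-width for the standardised difference is about 0.62 with the follow-up t test and 0.55 with ANCOVA at r = 0.5 (0.45 at r = 0.7). If a small effect means 0.2 SD (an assumption, since the article gives no number), power is 9.7% against 11.1% at r = 0.5. Adjustment does not turn this pilot into a dependable source of an effect size. That stands too. It limits the importance of the point but is no reason to leave unused a covariate that is already collected.

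It can also be said that a fuller analysis plan might add adjustment. That is weak here: the section presents its subsections as the detailed plan for each aim, and for Aim 2 it fixes a named test.

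A reader might go further and infer that baseline imbalance passes whole into the effect size, that the t test discards the baseline whatever scores it is run on, or that the estimate is biased. The documents do not support these readings. Only the fraction r, or -(1-r), of a gap carries through. A change-score test would use T1, and the article does not say which form is meant. Allocation is random, so imbalance adds noise around the right value.

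**Conclusion.** The point holds as one of efficiency: the planned test is valid, but a baseline-adjusted comparison would be more precise in either form that the t test might take. The improvement is about 23% of the variance against follow-up scores at an assumed r = 0.5, and anywhere from 7% to 48% over the range 0.3 to 0.7. Against change scores the large-sample figure runs from 35% down to 15% over the same range. That ANCOVA is better is secure throughout this range. How much better is not, because it rests on an r that the documents do not supply, on 30% attrition spread equally over the arms, and on equal SDs at T1 and follow-up. A correction worth making, not a threat to the validity of the trial.

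**What to change.** Replace the Aim 2 t test with wording such as: 'Each follow-up score will be compared between arms by ANCOVA, adjusting for the T1 value of the same scale: HADS-A, HADS-D, PCL-5 and MHSE at T2 and at T3, and SF-12 at T3. The adjusted difference will be reported with its 95% confidence interval and with a standardised effect size based on it, naming the SD used.'

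SF-12 is limited to T3 because Table 1 does not collect it at T2.

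For the scales measured at both follow-up visits, a mixed model with T1 score, arm, visit, arm-by-visit and T1-by-visit is an acceptable alternative. It should not be described as equivalent: with 30% attrition it uses participants seen at only one follow-up visit, whom a visit-by-visit ANCOVA omits at the visit they miss.

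The cost is a short change to the Aim 2 text. Data, visits and software stay the same.
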